### Adverse event recording

Serious adverse events are not anticipated in the study; therefore, any event will be recorded as an unexpected adverse event. We will record the following events: a significant (as reported by treating health professional) increase in anxiety symptoms, a significant (as reported by treating health professional) increase in low mood or depressive symptoms, suicidal ideation, physical or emotional harm resulting from additional investigations or healthcare services received, unnecessary physical investigations, any safeguarding concerns, or any other significant event. The chief investigators will immediately review serious events in accordance with the trial protocol and respond in accordance with relevant NHS protocols. We will report all serious events to the sponsoring NHS Trust and the reviewing REC as per the standard operating procedure of the sponsoring NHS Trust.

Newcastle University and Cumbria, Northumberland, Tyne, and Wear Foundation Trust have indemnified the trial.

### Sample size justification

The sample size of 200 was chosen based on the number of participants that could be recruited given the funding envelope and time available. This number compares favourably with previous health checks trials that found a difference between groups [12]. Assuming an attrition rate of 10%, the sample size was inflated to 220 (110 per arm).

### Data analysis plan

#### Statistical analysis for quantitative analysis

We will carry out all statistical analyses in accordance with the intention-to-treat principle where all participants’ outcomes are analysed as randomised. We will report all participant flow in accordance with CONSORT statement for non-pharmacological interventions. A full statistical analysis plan will be written and signed-off before trial statisticians receive any unblinded data. The following represents a summary of the planned analyses.

The underlying structure of the data displays a two-level hierarchical structure, in which one level (participants) is nested within another (practices). Members of the same practice share contextual factors and GP conduct, meaning 2 people of the same practice are more likely to have similar data relative to two people from different practices. This clustering effect can be measured using the intra class correlation coefficient (ICC). To compare the groups for the primary outcome, taking into account the clustering effect, we will use a mixed-effects Poisson regression model that has fixed effects for cluster size, treatment allocation, age, and sex. If this model does not converge, we will reduce the number of fixed effects in the model and then (if it still does not converge) change the random cluster effect to a fixed effect.

We will conduct subgroup analyses for the primary outcome by including the subgroup variable and an interaction parameter between subgroup variable and intervention. The subgroups we will investigate are number of conditions at baseline (above median vs median or below) and presence vs absence of mental health condition at baseline.

For secondary outcomes, we will use appropriate mixed-effects regression models, depending on the outcome type. If the outcome is a questionnaire that is also assessed at baseline, the model will adjust for that baseline measure.

Participants who withdraw consent for the collection of routinely available data prior to month 9 will not be included in the primary outcome analysis. We do not anticipate there being missing data for the primary outcome as it is based on routinely collected data. Secondary analyses will be complete-case analyses. For outcomes that are significant, if there is substantial differential dropout between treatment groups, we will apply multiple imputation with at least 20 imputed datasets and undertake sensitivity analyses to explore the robustness of results to the missing not at random assumption. We will record and tabulate the number of serious adverse events per group.

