#### Outcome measures

The primary outcome for the trial will be the incidence of new health needs or conditions detected and met at 9 months. The primary analysis will report the mean number of identified needs that are met for each group. A number of secondary outcomes will also be evaluated including the following: the extent of health monitoring and health promotion needs met at 9 months, the incidence of social needs identified at 9 months, change in participant or carer general health, changes in quality of life, and changes in primary and secondary health and social care resource usage and costs. The primary economic outcome will be the incremental cost per QALY gained at 9 months.

Effectiveness measures:Bespoke Health Records Data Collection Form: we will collect health and social data routinely recorded by practices alongside information about previous health checks and health screening. This was informed by data collection from Cooper et al. [12] and includes the following: short and medium term health outcomes including number and type of new health needs/new conditions/new manifestation of an existing or previously diagnosed condition identified, any referrals to secondary care and/or general hospitals and results, screening or treatments undertaken (including management of Quality & Outcomes Framework qualifying long term conditions and review of medications or other treatment plans), and whether these health needs/conditions were resolvedPrimary Care Outcomes Questionnaire (P-COQ [29]) is a standardised 24-item questionnaire to measure outcomes in primary care. Analysis has identified 4 domains (health and wellbeing, health knowledge and self-care, confidence in health provision, and confidence in health plan) with high levels of internal consistency across each domain (Cronbach’s *α* = 0.77–0.95) and correlate with comparator Patient-Reported Outcome Measures (PROMs)Bespoke Lifestyle Outcomes Questionnaire gathers information about lifestyle choices and health related behaviours

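### If counts of new met needs are overdispersed within practices, the Poisson model with only a practice random effect makes the two subgroup interaction tests too liberal

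*Protocol article*

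**What the plan says.** The outcome is a count per person. Under Outcome measures the article says: "The primary analysis will report the mean number of identified needs that are met for each group".

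Under Statistical analysis for quantitative analysis it names the model: "To compare the groups for the primary outcome, taking into account the clustering effect, we will use a mixed-effects Poisson regression model". The fixed effects are allocation, age, sex and cluster size. The data are described as having two levels, participants within practices, so practice carries the only random effect. If the model does not converge, fixed effects are to be removed; if it still does not converge, the analysts will "change the random cluster effect to a fixed effect". No step is tied to the dispersion of the counts.

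Subgroup analyses of the primary outcome are to be done by "including the subgroup variable and an interaction parameter between subgroup variable and intervention". The subgroups are "number of conditions at baseline (above median vs median or below) and presence vs absence of mental health condition at baseline". Both are characteristics of the person, so both vary within a practice.

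**The concern.** A practice intercept can take up extra variation only as differences between practices. That protects a contrast between practices, such as treatment. It does nothing for a contrast between people in the same practice, and a subgroup-by-treatment interaction is largely of that kind. If residual counts vary more than a Poisson distribution allows, the interaction standard error is too small. The variation that the practice intercept does absorb raises the estimated practice variance.

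The article gives reasons to expect such variation. Apart from final-stage terminal illness, eligibility sets no limit on morbidity. One appointment of about 45 minutes covers many domains, so needs may be found in batches. The intention-to-treat comparison will include people who do not attend. Neither baseline subgroup variable is a covariate in the main model.

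At stake is the false-positive rate of two prespecified tests on the primary outcome. The stated fallback would not catch the problem, because an overdispersed Poisson model usually converges, and its last step keeps the Poisson variance.

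**Working it through.** **Inputs from the article.** Count outcome; Poisson model with a practice random effect; two person-level interactions; 200 participants (Sample size justification). The only design figure that can be reproduced is the inflation for 10% attrition: 200 × 1.10 = 220. (Dividing instead gives 200/0.90 = 222.2, so 223; this has no bearing here.)

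**Assumptions, because the article gives no figure.** Two-sided 5% level; mean count 2 or 5; within-practice variance/mean ratio φ from 1 to 3; 10, 20 or 40 practices; log-scale practice variance 0, 0.05 or 0.2; subgroup prevalence 50%.

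**Step 1: what the ratios mean.** If people differ in their underlying rate with coefficient of variation CV, then φ = 1 + mean × CV². At a mean of 2, CV 0.5 gives 1 + 2 × 0.25 = 1.5, and CV 0.71 gives 1 + 2 × 0.50 = 2.

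**Step 2: approximation.** For a within-practice contrast the true standard error is √φ times the reported one, so the null rejection rate is 2 × [1 − Φ(1.96/√φ)]. At φ = 2: 1.96/1.414 = 1.386, which gives 16.6%.

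**Step 3: simulation.** 1000 null trials per scenario, N = 200, gamma-Poisson counts for people within log-normal practices. The stated model was fitted by maximum likelihood with Wald z tests. The Monte Carlo standard error is about 0.7 points at 5% and 1.2 points at 17%. The log-scale ICC is σ²/(σ² + ln(1 + 1/mean)) as estimated from the Poisson fit. Its true value is σ²/(σ² + ln(1 + φ/mean)); at φ = 2 and mean 2 this is 0.05/(0.05 + 0.693) = 0.067.

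Results with 20 practices, mean 2, true practice variance 0.05:

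| φ | Interaction, approximation | Interaction, simulated | Main treatment test | Estimated practice variance | ICC, estimated vs true |
|---|---|---|---|---|---|
| 1 | 5.0% | 4.9% | 9.9% | 0.035 | 0.075 vs 0.110 |
| 1.2 | 7.4% | 7.8% | 9.6% | 0.043 | 0.092 vs 0.096 |
| 1.5 | 11.0% | 10.5% | 8.0% | 0.056 | 0.115 vs 0.082 |
| 2 | 16.6% | 17.2% | 8.6% | 0.079 | 0.156 vs 0.067 |
| 3 | 25.8% | 26.9% | 9.7% | 0.124 | 0.223 vs 0.052 |

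**Step 4: sensitivity of the interaction rate.**
- Mean 5: 15.9% at φ = 2 and 24.9% at φ = 3.
- φ = 2, mean 2, with 10 or 40 practices: 16.1% and 17.1%.
- φ = 2, mean 2, 20 practices, true practice variance 0 or 0.2: 18.4% and 19.5%.

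So φ drives the result and the unstated number of practices hardly matters.

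**Step 5: sensitivity of the practice variance.** At φ = 2 and mean 2, the estimate against a true 0.05 is 0.049 with 10 practices (ICC 0.100 vs 0.067) and 0.129 with 40. With 20 practices and a true value of zero, it is 0.036 (ICC 0.078).

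**Step 6: two tests together.** If independent, the chance of at least one false positive is 1 − 0.895² = 19.9% at φ = 1.5 and 1 − 0.828² = 31.4% at φ = 2, against 1 − 0.95² = 9.75% nominally.

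**Step 7: negative binomial mixed model, 20 practices, practice variance 0.05.** Interaction rejection is 5.0%, 5.7% and 6.6% at φ = 1.5, 2 and 3 (mean 2), and 5.2% at φ = 3 (mean 5). Mean estimated practice variance is 0.031 to 0.034 against a true 0.05: no longer inflated, but with the usual downward bias of maximum likelihood. The simulated data are gamma-Poisson, so this model is correctly specified here. The Poisson model with a participant-level random effect was not simulated.

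**The case against.** The strongest reply is that the article calls its analysis section a summary and promises a full statistical analysis plan, where a dispersion check could appear. That stands in part: the unseen plan may already deal with this. But the article does not merely leave the model open. It names the distribution and the level of clustering, and its fallback would not respond to overdispersion.

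Second, the article gives no dispersion figure. The outcome is new needs that are also met, which existing morbidity need not drive, and batching at one appointment applies only to the health check arm. Age, sex and, in its own model, the subgroup variable will explain some of the heterogeneity, so φ must be read as residual dispersion. All of this stands. It is why the point is conditional and the mild case, φ = 1.2, is shown.

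Third, a reader might infer that the primary comparison itself is compromised. The results do not support that: the main test rejects in 9.9% of null trials at φ = 1 and 9.7% at φ = 3. Its excess over 5% comes from a Wald test with an assumed 20 practices, which is a different matter.

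Fourth, a reader might infer that a misleading ICC will be published, or that subgroup results will decide who is offered the check. The article says only that clustering can be measured by the ICC and promises no report of it. It ties later provision to the check being effective overall (Dissemination plan; Significance).

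**Conclusion.** The point holds conditionally. As written, the model cannot carry person-to-person overdispersion, and the two subgroup interaction tests would bear the consequence. The error is nil at φ = 1, small at 1.2 (about 8% against 5%), about double the nominal rate at 1.5, and about 17% and 27% at 2 and 3. Overdispersion is plausible for counts of health needs, but the article does not demonstrate it, so the stronger statement that these tests will reject far too often is not supported.

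Overstatement of the practice variance and ICC is also conditional. With 20 practices it appears from φ of about 1.5. At 1.2 the downward bias of maximum likelihood offsets it. With 10 practices and φ = 2 the variance is about right although the ICC is still too high.

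These sizes rest on the assumed means, practice variances, numbers of practices, subgroup prevalence and two-sided 5% level.

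**What to change.** For the primary outcome and its subgroup analyses, specify a negative binomial mixed model with a practice random intercept and the same fixed effects. A Poisson model with an added participant-level random effect is the alternative. Keep the stated Poisson model as a sensitivity analysis. If the statistical analysis plan is already signed without such a term, report the observed dispersion and give the negative binomial results beside the Poisson ones for the subgroup tests and for any practice variance or ICC that is presented.

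The cost is a change of wording and one extra parameter. Interaction intervals widen by roughly √φ: √1.5 = 1.22, √2 = 1.41 and √3 = 1.73, that is 22%, 41% and 73%. This is not a small change where dispersion is marked, but it reflects uncertainty that the Poisson intervals leave out. With no overdispersion there is little change.

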### Participant identification and recruitment process

Participating practices will identify autistic adults to send a study information pack explaining the study and inviting participation. For those people unable to consent for themselves, the study information pack will be sent to a relative or carer (referred to as a ‘consultee’ in the Mental Capacity Act), asking them to advise whether the person should take part. The autistic adult or their consultee will then be asked to complete the measures from the perspective of the autistic adult. Easy read and short versions of all information sheets are available to possible participants. Interested autistic adults will complete an expression of interest form and send this to the research team. A member of the research team, RDN staff, or primary care staff will arrange a meeting with the prospective participant to discuss the trial in more detail and take informed consent using face to face, video, or telephone means, in line with the participant’s preference. See Appendix 1 for copies of the consent forms. After informed consent, the research team, RDN staff, or primary care staff will collect baseline data on participants. See Fig. 1 for the flow chart of trial procedure.

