### Randomisation

Practices will be randomised to the intervention (health check) arm or the control (usual care) arm prior to participant recruitment via computer-generated sequence blocks [2, 4, 23]. Randomisation will be stratified by practice list size (small < 10,000 and large ≥ 10,000). A member of the research team independent of trial data collection will oversee this process and inform the practices of the randomisation outcome. The research team will make autistic participants aware as to whether they are in the health check or usual care arm in the study information pack. Due to the design of this trial, it is not possible for practices or participants to remain blinded to group.

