#### Baseline characterisation

Following informed consent, participants will complete baseline measures (on paper or online via Qualtrics software [25]). These comprise a set of self-report measures to enable characterisation of the individual’s autism profile, general ability, and demographics. Participants can choose to complete the measures independently or with support from a carer or supporter or the person taking consent (researcher, RDN staff, or primary care staff). The following self-report measures will be collected:Demographics: we designed a bespoke demographic questionnaire for the study with versions for autistic adults, carers and supporters, health professionals, and administrate staff. The autistic adult’s version includes questions about personal characteristics, their living situation, employment and education, learning ability, support needs, and health conditions. For other participants, demographic information about personal characteristics is collectedSocial Responsiveness Scale – Second Edition (SRS-2) [26] is a 65-item standardised self-report questionnaire used extensively to rate the social communication features of autistic adults and children. Reported estimates of internal consistency between 0.94 and 0.96 and predictive validity of the adult form found a specificity level of 0.60 and sensitivity of 0.86 [27]Waisman Activities of Daily Living Scale (W-ADL) [28] is a measure of independence validated in people with a broad range of developmental disability diagnoses. Analysis indicates that it is reliable over time (*κ* = 0.92–0.93), with high levels of internal consistency across disability groups (Cronbach’s *α* = 0.88–0.94) and criterion validity when compared to the Vineland Screener Adaptive Behavior Composite Score (*r* = 0.78)

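### The primary model leaves out baseline morbidity although participants join knowing their arm, and its cluster-size term is undefined

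*Protocol article*

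**What the plan says.** All references are to the protocol article.

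- **Primary model** (Statistical analysis for quantitative analysis): a "mixed-effects Poisson regression model that has fixed effects for cluster size, treatment allocation, age, and sex", with practice as the random effect.
- **Subgroups** (same section): "number of conditions at baseline (above median vs median or below) and presence vs absence of mental health condition at baseline". Each is fitted as a main effect plus an interaction with treatment. Neither variable is in the main model.
- **Baseline adjustment elsewhere** (same section, on secondary outcomes): "If the outcome is a questionnaire that is also assessed at baseline, the model will adjust for that baseline measure". No equivalent rule covers the primary outcome.
- **Stratification** (Randomisation): "Randomisation will be stratified by practice list size (small < 10,000 and large ≥ 10,000".
- **Order of events** (Randomisation): "Practices will be randomised to the intervention (health check) arm or the control (usual care) arm prior to participant recruitment". The research team will also "make autistic participants aware as to whether they are in the health check or usual care arm in the study information pack".
- **Who invites** (Participant identification and recruitment process): "Participating practices will identify autistic adults to send a study information pack explaining the study and inviting participation". Under Recruitment and eligibility criteria, a GP may also withhold an invitation that they judge inappropriate.
- **Baseline data** (Baseline characterisation): the demographic questionnaire, completed after consent, covers "their living situation, employment and education, learning ability, support needs, and health conditions", among other items.

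**The concern.** Randomising practices balances practices in expectation. It does not balance the people who enrol when both the practice making the selection and the person deciding to join know the arm. Someone offered a health check of about 45 minutes may weigh the invitation differently from someone offered usual care, and health status is an obvious characteristic on which the two groups could differ. The outcome is a count of new health needs detected and met. The health-records form also captures new manifestations of existing conditions, so a link between existing morbidity and the count is plausible. A difference in case-mix could then appear as a treatment effect, or hide one. None of the listed covariates measures health.

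The second issue is the term *cluster size*. In cluster trials it often means the number of participants per cluster. Here recruitment follows allocation and is arm-aware, so allocation can change that number. On that reading the model conditions on a post-randomisation quantity and omits the factor used to stratify.

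**Working it through.** **What the plan lets us reproduce.** The plan gives no figure on this point. It states no effect size, ICC, number of practices or mean count, so every input below is assumed unless marked otherwise.

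**1. Spurious rate ratio with no true effect.** Formula: exp(β × d), where β is the log-rate slope per SD of baseline conditions and d is the arm difference in SD.

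| β | d = 0.25 | d = 0.35 |
|---|---|---|
| 0.2 | exp(0.05) = 1.05 | exp(0.07) = 1.07 |
| 0.4 | exp(0.10) = 1.11 | exp(0.14) = 1.15 |

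If the sicker people join the usual care arm instead, the ratios invert, to about 1/1.05 = 0.95 down to 1/1.15 = 0.87.

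**2. Chance imbalance for comparison.** The article plans about 100 participants per arm. With an assumed design effect (DE) of 1 to 1.5, the SE of the arm difference is √(2/100 × DE) = 0.141 to 0.173 SD. An imbalance of 0.25 SD is therefore 0.25/0.173 = 1.4 to 0.25/0.141 = 1.8 standard errors, and could arise without any selection.

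**3. Precision.** The share of treatment-effect variance removed by adjustment is (β²/m) / (s² + (1/μ + 1/k)/m). Here s = 0.25 is the between-practice SD on the log scale. The term 1/k = 0.33 is the overdispersion between people, taken to include the part due to morbidity. The mean count μ is 1.5 to 3, and m is 7 to 10 participants per practice.

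- Low corner (β = 0.2, μ = 1.5, m = 10): 0.0040 / (0.0625 + 0.0997) = 0.025.
- High corner (β = 0.4, μ = 3, m = 7): 0.0229 / (0.0625 + 0.0948) = 0.145.

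The standard error falls by 1 − √0.975 = 1.3% to 1 − √0.855 = 7.5%.

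**4. Null simulation, as a check on direction.** Settings: 200 participants, 20 or 40 practices, mean count 2, practice SD 0.2, baseline conditions Poisson with mean 3, and 300 runs per cell. Poisson GEE with bias-reduced standard errors stood in for the mixed model.

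- *Slope 0.2 per condition, arm difference 0.5 conditions.* The SD of the count is √3 = 1.73, so this is a slope of 0.35 per SD and an imbalance of 0.29 SD, inside the range used above. Type I error without adjustment was 8.7% (20 practices) and 15.7% (40 practices). With the count in the model it was 4.3% and 4.7%.
- *Slope 0.1, difference 0.5.* The unadjusted rates were 5.7% and 7.7%. With a Monte Carlo SE of about 1.3 points, these are not clearly above 5%.
- *Slope 0.2, difference 1.0* (0.58 SD, outside the range above). The unadjusted rates were 29% and 32%.

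Adjustment works here by construction, because the simulated selection acts only through the measured count.

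**5. The two readings of *cluster size*.**

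| Reading | Stratum in the model? | Affected by allocation? | Consequence |
|---|---|---|---|
| Participants recruited per practice | No | Possibly | Post-randomisation covariate; stratifier omitted |
| Practice list size | Yes, in substance | No | Wording only |

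No section of the article settles which is meant.

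**The case against.** - **The article is a summary and a full SAP is promised.** This stands for definitions that a SAP would normally supply. It does not dispose of the covariate list, which the article states explicitly.
- **Cluster size may simply mean practice size.** The clusters are practices, list size is the only practice attribute used in randomisation, and the qualitative sampling also contrasts large with small practices. This stands. A reader might infer that the model has replaced the stratum with a post-randomisation variable, but the text does not establish that.
- **Morbidity is partly handled.** The subgroup models contain the morbidity variable and its interaction with treatment. That is true, but those are separate analyses and the main estimate remains unadjusted.
- **A condition count is not unmet need.** Someone with few diagnoses and poor access to care may have the most undetected need. This stands: neither the sign nor the size of the association can be taken from the article. A reader might assume that baseline morbidity is the strongest available predictor, and nothing in the article supports that.
- **The confirmed baseline source is self-report by people who already know their arm.** This stands, and it affects which source to use.
- **The median split.** A reader might call the cut at the median an error. It is prespecified, and adding a continuous interaction beside it is an optional refinement.

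**Conclusion.** The point holds with moderate confidence, as an inexpensive improvement to the primary model. Recruitment is arm-aware by design, the stated covariates contain no measure of health, and a relevant measure is collected and already used for subgroups. The cluster-size limb supports only a request to define the term and reconcile it with the Randomisation section.

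The spurious rate ratio of about 1.05 to 1.15 and the variance reduction of about 2.5% to 14.5% rest entirely on assumed slopes, imbalances, counts and practice variation. They show what could happen. They do not estimate this trial's bias, and the article contains no evidence that the arms actually differ. At the low end the gain in precision is negligible.

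**What to change.** Make the change in the SAP, which the article says will be signed off before the trial statisticians receive unblinded data. Recruitment closed on 21 March 2024 (Trial status), so the remedy has to be analytic.

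1. Replace *cluster size* with the list-size stratum (below 10,000, or 10,000 and above) as the fixed effect. This is right on either reading of the term.
2. Add baseline number of conditions (continuous, for example log(1 + count)) and baseline mental health condition as prespecified fixed effects in the primary model.
3. Take both from pre-baseline health records if these are extracted. Otherwise use the baseline questionnaire, and state that it was completed after the arm was known, so that reporting could itself differ by arm.
4. State that the adjustment corrects only for measured morbidity.

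The cost is SAP wording and two extra parameters. The questionnaire data are already part of the trial. The article does not confirm that a baseline condition count is extracted from records, so that source may need additional work.

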## Methods and design

### Study design

This study is a two-group cluster RCT non-blinded to participants but blind to the outcome assessors. Primary healthcare services (National Health Service general practices, referred to as ‘practices’ from hereon) will be randomised to either deliver the health check for autistic adults (intervention arm) or provide usual care (control arm), in keeping with previous research methods from published research, and following discussion with autistic people during the research design stage. We will offer adults aged 18 years or above with a clinical diagnosis of autism spectrum disorder at participating practices the opportunity to take part. We will administer assessments on entry to the trial (baseline) and at 3 months, 6 months, and 9 months after the health check, for the intervention arm, or after baseline measures are completed, for the usual care group. We will also gather qualitative data on the acceptability and feasibility of the health check to inform its future use. See Additional File 1 for Standard Protocol Items: Recommendations for Interventional Trials (SPIRIT) checklist for study.

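### The last-resort non-convergence rule, fixed practice effects in place of random ones, cannot estimate the treatment effect because practices are the randomised units

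*Protocol article*

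**What the plan says.** The relevant text is in three sections of the protocol article.

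- **Study design**: "This study is a two-group cluster RCT non-blinded to participants but blind to the outcome assessors". No crossover or stepped period is described.
- **Randomisation**: "Practices will be randomised to the intervention (health check) arm or the control (usual care) arm prior to participant recruitment". Nothing in the article allows both allocations within one practice.
- **Statistical analysis for quantitative analysis**: the cluster is the practice, and the primary outcome is analysed with a "mixed-effects Poisson regression model that has fixed effects for cluster size, treatment allocation, age, and sex", plus a random practice effect. Two steps follow for non-convergence. The first is "If this model does not converge, we will reduce the number of fixed effects in the model", without saying which effects go. The second, if the model still fails, is to "change the random cluster effect to a fixed effect". No constraint or alternative estimator accompanies the second step.

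The same section calls itself a summary and says a full SAP will be signed off before the trial statisticians receive unblinded data.

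**The concern.** A fallback is written in advance so that the primary comparison survives if the preferred model fails. This one removes the comparison. In a parallel cluster trial, all information on treatment lies between practices, and fixed practice effects absorb all between-practice differences. Nothing is left from which to estimate treatment.

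If the step were reached, the trial would have no valid prespecified estimate for its primary outcome. The analyst would see no treatment effect, or would see one that looks like a result but is not an arm comparison. Any replacement would then be chosen after the planned model had failed.

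**Working it through.** **Inputs.** From the article: practice is the unit of allocation and the cluster; the fixed effects are treatment, cluster size, age and sex; the target is 200 participants. The only computed figure in the article is the inflation to 200 × 1.10 = 220; it reproduces, and nothing below depends on it. The number of practices K is not given, so 10, 20, 30 and 40 are tried as assumptions.

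**Step 1: algebra.** Let D_ij = 1 if participant i belongs to practice j. Because practices are allocated whole,

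T_i = Σ D_ij over the intervention practices.

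With fixed practice effects the linear predictor is η_i = Σ α_j D_ij + β T_i + other terms. For any number c, replace β by β + c and α_j by α_j − c in every intervention practice. Each η_i is unchanged, so the likelihood is unchanged, and the data cannot distinguish one β from another. The same holds for cluster size, since S_i = Σ s_j D_ij.

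**Step 2: rank.** The full fallback model has an intercept, K − 1 practice indicators, treatment, cluster size, age and sex, so K + 4 columns. Treatment and cluster size add no rank, so the rank should be K + 2. Numerical check with 200 participants in practices of uneven size:

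| K (assumed) | Columns | Rank | Rank, practice only | Rank, practice + treatment |
|---|---|---|---|---|
| 10 | 14 | 12 | 10 | 10 |
| 20 | 24 | 22 | 20 | 20 |
| 30 | 34 | 32 | 30 | 30 |
| 40 | 44 | 42 | 40 | 40 |

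The residual sum of squares of treatment regressed on the practice indicators is zero to machine precision (about 1e-26 or smaller).

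**Step 3: does dropping covariates help?** Remove cluster size, age and sex. The model has K + 1 columns and rank K (for K = 20: 21 columns, rank 20). Treatment is still aliased.

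**Step 4: what software might print.** One data set was simulated with 20 practices of 10, a true rate ratio of exp(0.4) = 1.49 and a between-practice SD of 0.4 on the log scale, all assumed. A Poisson model with fixed practice effects was fitted 100 times, once for each choice of one omitted practice per arm (10 × 10). The treatment rate ratio ran from 0.27 to 8.10, and the log-likelihood was −347.54 every time. Each value compares only the two omitted practices.

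**Step 5: is treatment estimable by another route?** Without practice indicators, the columns for intercept, treatment, cluster size, age and sex have full rank (5 of 5) for every K tried. On the same simulated data, a GEE with exchangeable correlation (treatment only) gave one answer: rate ratio 2.16, SE of the log rate ratio 0.22. That is (ln 2.16 − 0.4)/0.22 ≈ 1.7 standard errors from the assumed truth, and it does not depend on coding.

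**The case against.** The strongest reply is that this is a second-stage fallback. Treatment is estimable in the planned mixed model, and the rule applies only if that model fails and fails again with fewer covariates. This stands. A reader might infer that sparse counts and a near-zero practice variance make the step likely. The article does not support that: a near-zero variance often gives a boundary estimate and not a failed fit. In 400 trial fits of a random-intercept Poisson model (20 or 30 practices assumed, mean count 1.5, equal clusters, one bounded optimiser) none failed. At a true practice SD of 0, 68% to 76% reached a near-zero variance and still converged. Other software, overdispersed counts or very unequal practices might behave differently, and these were not tested.

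A reader might also infer a specific false-positive rate. Under no effect, the two-practice contrast can be declared significant in 8% to 31% of simulated trials, but only with an assumed practice SD of 0.25 and a variance-to-mean ratio of 1 to 3. With Poisson counts and a practice SD of 0 to 0.05 the rate is about 4% to 5%. With a ratio of 3 and little or no practice variation it is 21% to 26%; the large-sample value is 2 × [1 − Φ(1.96/√3)] ≈ 26%. That part is a separate question of overdispersion. The article supplies none of these inputs, so no error rate should be attached to this rule.

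Third, the article names no software. If treatment is the dropped term, no false result can be reported. Constraining practice effects to sum to zero within each arm would yield an arm contrast. But the text specifies no such constraint, the contrast concerns only the sampled practices, and its standard error omits between-practice variation, although the section says clustering will be taken into account.

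Last, the section is a summary and a SAP is to follow. That says where to make the correction. It does not make the stated rule right, and a SAP that copied it would inherit the defect.

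**Conclusion.** The point holds as a narrow one. As written, the final non-convergence step gives a model in which the treatment effect is not identified. This is algebraic: it needs only allocation by whole practice and unconstrained practice indicators beside treatment, which is the natural reading of the text. It does not depend on the number of practices, cluster sizes, outcome data or the covariates dropped first. The 0.27 to 8.10 range shows how arbitrary a printed coefficient could be in one assumed data set and does not predict this trial.

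The first-line analysis is unaffected, and the probability of reaching the step is unknown. It would be wrong to conclude that the primary analysis is invalid. This is a prespecified safeguard that would not work, worth correcting because it governs the only planned primary comparison if the mixed model fails.

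**What to change.** Delete the fixed-effect step and, in the SAP before unblinding, name a fallback in which treatment is estimable and clustering is respected. Either of these would serve:

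- a log-link GEE clustered on practice, with a small-sample-corrected robust variance; or
- a practice-level summary analysis comparing practice rates by arm, with degrees of freedom based on the number of practices.

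These are examples, and another valid marginal or cluster-level method would do. The cost is one sentence, with no extra data and no change to trial conduct.
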